## Abstract

**Background:**

Major depressive disorder (MDD) is a recurrent psychiatric condition that presents challenges in responding to treatment and achieving long-term remission. To improve outcomes, a shared decision-making treatment approach with patient and healthcare practitioner (HCP) engagement is vital. PatientsLikeMe (PLM), a peer community of patients, provides information on MDD, symptoms, and treatment through forums and resources, helping patients stay engaged in their treatment journey. Data on PLM can be harnessed to gain insights into patient perspectives on MDD symptom management, medication switches, and treatment goals and measures.

**Methods:**

This ongoing, decentralized, longitudinal, observational, prospective study is being conducted using the PLM platform in two parts, enrolling up to 500 patients with MDD in the United States aged ≥ 18 years to compare vortioxetine with other monotherapy antidepressants. The first qualitative component consists of a webinar and discussion forum with PLM community members with MDD, followed by a pilot for functionality testing to improve the study flow and questions in the quantitative survey. The quantitative component follows on the PLM platform, utilizing patient-reported assessments, over a 24-week period. Three surveys will be conducted at baseline and weeks 12 and 24 to collect data on patient global impression of improvement, depression severity, cognitive function, quality of life (QoL) and well-being, medication satisfaction, emotional blunting, symptoms of anhedonia and resilience, as well as goal attainment. Quantitative results will be compared between groups. The qualitative component is complete; patient recruitment is underway for the quantitative component, with results expected in late 2023.

**Discussion:**

These results will help HCPs understand patient perspectives on the effectiveness of vortioxetine versus other monotherapy antidepressants in alleviating symptoms of MDD and improvements in QoL. Data from the PLM platform will support a patient goal-based treatment approach, as results can be shared by patients with their HCPs, providing them with insights on patient-centric goals, treatment management and adherence, as well as allowing them to observe changes in patient-related outcomes scores. Findings from the study will also help to optimize the PLM platform to build scalable solutions and connectivity within the community to better serve patients with MDD.

## Background

Depression is one of the largest causes of disability, accounting for a global disease burden of 4.3% [1]. Major depressive disorder (MDD) is the most prevalent and debilitating mental health disorder worldwide [2]. As of 2020, an estimated 21 million adults in the United States (US) had at least one major depressive episode, which represents 8.4% of all US adults [3]. The economic burden of MDD in the US is an estimated $326 billion, of which treatment cost is estimated to constitute only about 11% of that amount. The biggest contributors to this burden are comorbidities, mortality, and MDD-related workplace costs [4, 5]. The high rate of impairment caused by MDD, which includes poor health conditions, comorbidities, and mortality, is an issue of urgent concern for the US population [6]. Symptoms of MDD, such as the inability to maintain relationships and engage in leisure activities, are disabling for the patient, significantly impairing their daily life and functioning [7]. Emotional symptoms, such as depressed mood and anhedonia, are often accompanied by cognitive and physical dysfunction [8].

Despite clinical and therapeutic advances over the years, a large proportion of patients treated with antidepressants continue to face challenges in responding to treatment or achieving remission. Patients often require multiple treatments to find any benefit, and those with a greater number of different therapies can be more resistant to treatment [9]. These challenges often arise as a result of treatment approaches that seek acute symptomatic relief rather than the achievement of a long-term solution [9]. In addition, the definition of remission in MDD usually encompasses only traditional constructs such as sadness, anhedonia, and pessimistic thoughts. However, patients often perceive improvement in other outcomes, such as psychosocial and occupational functionality, as more meaningful [10–13].

Treatment nonadherence is another major challenge and may be due to varying education levels, side effects, poor interaction between the patient and healthcare provider (HCP), and culturally induced negative attitudes toward mental illness [14]. Furthermore, residual symptoms that persist despite antidepressant therapy can increase the risk of relapse and recurrence [15]. Recent literature has emphasized the need for an integrative and collaborative care approach to mitigate some of these issues and improve the treatment paradigm for patients with MDD [4].

### Measurement-based care (MBC) and shared decision-making (SDM)

The American Psychiatric Association provides clinical guidelines that recommend MBC for overcoming some of the challenges of treating depression. MBC can potentially enhance quality of care and improve clinical outcomes by including evaluations of quantitative symptom measures, level of functioning, and quality of life (QoL) [16]. MBC provides a systematic framework for evidence-based practice in monitoring routine outcomes and has shown significant benefits in treating a range of psychiatric disorders. Specifically, MBC allows clinicians to individualize treatment based on the patients’ symptoms and severity, identify non-responders, detect residual symptoms, and encourage treatment adherence through better patient engagement [17, 18].

Typically, MBC is characterized by routine administration of validated scales with scores that provide clinician- or patient-reported outcomes (PROs). These scores are used to inform SDM during treatment management [17], promoting clinician-patient engagement and encouraging patients to actively participate in their care, thus influencing treatment outcomes. Apart from better clinical outcomes, SDM positively affects patient satisfaction and adherence, measures increasingly considered to be part of treatment effectiveness [19].

One approach to SDM is for patients and clinicians to discuss individual treatment goals collaboratively. The Goal Attainment Scale adapted for Depression (GAS-D) is an instrument that provides a structured approach to setting and measuring progress toward the attainment of treatment goals. This allows for assessment of patient-centric goals that may not be captured with more traditional scales [10].

Patient engagement has been linked to better treatment outcomes, helping patients feel equipped, empowered, and enabled to deal with the challenges of MDD. In line with this, digital health platforms are low–resource-intensive, easily disseminated tools that help patients take ownership of their individual healthcare journeys [20]. Digital platforms have helped increase understanding of mental illness and may have a role in improving outcomes for patients with chronic mental health conditions. Real-time data obtained through these platforms can guide decision-making, course of treatment, and early intervention [21].

### PatientsLikeMe (PLM) platform

PLM is a web-based interactive digital health platform that is powered by patients and helps empower them to improve their lived experience. More than 850,000 members diagnosed with various conditions are members of PLM, including > 62,000 members with MDD, 50% of whom report MDD as a primary condition. The platform allows patients to share detailed computable information about their health, symptoms, treatments, and goals with other patients, and to learn from others’ experiences [22].

PLM is designed to help patients understand their conditions in the context of a peer-to-peer community. The PLM community gives patients with MDD a channel to receive education about their condition and what symptoms they can expect. It also provides information about available treatment options and offers a supportive arena to communicate with peers [22, 23]. The platform offers data-led intelligence to help patients better understand their health, identify treatment options, and nurture their shared journeys of healing. PLM enables patients to build resiliency and manage the complexity of their health, setting a new standard for holistic healing through personalized psychosocial interventions. PLM has helped patients make informed decisions, particularly about side-effect management, as observed through a cross-sectional online survey study, which demonstrated that patients were able to manage their symptoms better and experience greater benefit through PLM resources [19]. There is a vast amount of data available on PLM that can be harnessed to improve, design, and conduct trials in clinical and real-world settings [24]. These real-world research studies offer a way to understand PROs, quantify symptoms, and enable patient education and decision-making [22]. The key highlights of the PLM platform are presented in Fig. 1. PatientsLikeMe LLC receives research funding from various pharmaceutical and commercial partners and the site is free to use for members. However, PLM collaborates with pharmaceutical companies and medical device makers by offering research services using deidentified data.

**Fig. 1 Fig1:**
[figure not shown]
Key highlights of the PatientsLikeMe platform. Abbreviation: MDD = major depressive disorder

### Patient perspective in MDD treatment

To fully understand the subjective experience of MDD, it is vital to assess cognitive function in patients [25]. Cognitive dysfunction is common in patients with MDD; however, the clinical setting offers no formal tools to routinely check for cognitive ability. Thus, studies that collectively look at clinical remission along with subjective symptom improvement become key to meeting this need. Additionally, HCPs cannot fully account for patient experience because of the burdensome depression assessment process and the lack of SDM. It is essential to understand the patient’s perspective regarding their symptoms and priorities to establish meaningful improvement through treatment [25]. Platforms such as PLM can serve as a bridge to connect researchers with real-world patient evidence and perspectives, thus emphasizing the need for MBC and SDM.

The goal of this study is to understand the outcomes of MDD in patients treated with monotherapy antidepressants such as vortioxetine, employing SDM and a goal-setting approach. Vortioxetine is a multimodal antidepressant that has demonstrated efficacy, safety, and tolerability in adults for the treatment of MDD [26]. In addition, patients receiving vortioxetine have shown improvement in cognitive symptoms, functionality, and overall QoL, along with beneficial effects in other physical symptoms such as sexual dysfunction, sleep disturbances, anxiety, pain, and weight loss [27]. Improvements in these residual symptoms are often associated with patients achieving full recovery [27].

### Rationale and aim of the study

In this ongoing, observational, real-world, prospective, decentralized study, we aim to gain insight and better understanding of the treatment experience of patients living with MDD, including symptom management, side effects, medication switches, and any treatment goals. Patients are provided with assessments within the PLM platform that support MBC, potential SDM, and tools to help them track their health-related goals, such as mood, cognitive symptoms, emotional well-being, and function. The primary objective of the study is to assess Patient Global Impression of Improvement (PGI-I) scores with vortioxetine at 12 weeks compared with other monotherapy antidepressant treatments following a new start or switch. Secondary objectives include measurement of changes between groups in MDD symptoms and severity, cognitive function, well-being, emotional blunting, resiliency, medication satisfaction, QoL, goal attainment, and patient engagement using the PLM platform. Additional areas of exploration will focus on aspects of the patient journey, such as medication adherence, reason for switching medication, compliance, and barriers to treatment.

## Methods

### Study design

This ongoing, mixed-method, longitudinal cohort study, conducted in the PLM online patient community, analyzes overall improvement with vortioxetine at 12 weeks compared with other monotherapy antidepressants following a new start or switch of treatment using the PGI-I. This study consists of an initial qualitative educational webinar and a quantitative prospective analysis using patient-reported assessments along with goal setting and goal tracking over two 12-week periods (Fig. 2).

**Fig. 2 Fig2:**
[figure not shown]
Study design. Abbreviations: MDD = major depressive disorder; PLM = PatientsLikeMe; SOC = standard of care

### Qualitative study

The initial qualitative study was planned as a developmental phase, including a webinar and survey using the PLM platform, with a focus on usability, functionality, and value to the patient, which inform changes to the study flow and quantitative survey questions. The educational outreach webinar provided an overview of treatment and management of MDD in the PLM platform, followed by a discussion forum on MDD with 13 participants. The qualitative component included a functionality test with another 10 participants who were given an overview of the study and a walk-through of the study platform, including the quantitative survey and PROs. These patients were asked to provide feedback on components of the PLM platform related to study flow, usability of the platform, PLM engagement, and current health data tracking including new goal setting, goal-tracking features, and ways to improve the study flow and quantitative survey.

### Quantitative study

Three quantitative surveys at baseline, week 12, and week 24 will be conducted to collect the data. The quantitative survey uses the PLM platform to track important health information such as mood, well-being, cognitive impairment, function, QoL measures, and goal attainment. This platform also consists of patient-facing educational support and videos to set and track patient goals with their HCPs. A doctor visit guide is available for patients so they can relay important health information, as well as their goals and PROs, from the PLM platform to their care team, either electronically or face-to-face.

### Study population

This study will include up to 500 members of the PLM platform with MDD who are US residents aged ≥ 18 years. For the qualitative component of the study, 13 patients were enrolled into the webinar as well as in the question-and-answer (Q&A) portion of the qualitative analysis. An additional 10 patients participated in the testing of the survey instrument. At least 480 patients will be recruited for the quantitative survey so that a minimum of 378 patients can be evaluated at week 12 for the primary objective with targeted recruitment ratios of 2:1 for other standard of care (SOC) monotherapy to vortioxetine.

### Inclusion and exclusion criteria

This study consists of members of the PLM platform who have met the inclusion and exclusion criteria. Patients were included in the qualitative study group if they self-reported their MDD diagnosis on the PLM platform and are currently taking antidepressant monotherapy. For the quantitative study group, eligible patients must have a diagnosis of MDD by week 6, confirmed through an electronic medical record (EMR) in the PLM profile or physical medical records provided by the patient, or a clinical confirmation by the patient’s HCP. Patients without a confirmation of diagnosis will be excluded from the study. Additionally, patients in the quantitative group must have a baseline 9-item Patient Health Questionnaire (PHQ-9) score ≥ 5 and should have either recently started or changed antidepressant monotherapy within the last 90 days before consent. Patients with a reported diagnosis of bipolar disorder, schizophrenia, schizoaffective disorder, or post-traumatic stress disorder will be excluded from this study.

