##### PLM web-based assessments

Patient measures: A set of surveys including 6 assessment scales will be posted on the PLM platform to capture patient-rated measures of depression, response to therapy using the PGI-I, cognitive functioning using the 5-item Perceived Deficits Questionnaire–Depression (PDQ-D5), QoL using the 5-item World Health Organization Well-being Index (WHO-5), depression severity using the PHQ-9, and life satisfaction using the Quality of Life Enjoyment and Satisfaction Questionnaire–Short Form (Q-LES-Q-SF) (Table 1).

**Table 1 Tab1:** Patient assessments for primary and secondary outcomes

**Primary**	**Patient baseline reflection on current depression status (baselining for PGI-I)**

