For the qualitative analysis, themes arising from any free-text data were qualitatively evaluated and presented as frequencies in tables using a directed content analysis approach. A coding system for thematic analysis was created by PLM team members. The quantitative analysis will be summarized using descriptive statistics for patient characteristics by age, sex, condition-related characteristics, and treatments. For continuous variables, descriptive statistics will include the number of observations (N), mean and SD (mean, SD), median and interquartile range (median, [Q1, Q3]), and minimum and maximum values (min, max). For categorical variables, descriptive statistics will include the frequency and relative percentage of values in each category. Upon review of data, chi-square statistics will be used for categorical variables, while two sample *t*-tests and the analysis of variance procedure will be used to assess continuous variables between/among groups. To address confounding, various methods used in observational studies, such as stratification, corresponding to the levels of potential confounders (e.g., age groups and sex) will be employed as applicable. A multivariable regression analysis also will be used to control confounding. A total of 480 patients are planned to be recruited, to have at least 378 patients complete the week 12 survey after accounting for 15% of responders at week 12 (PGI-I < 2) and 20% attrition.

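### The week-12 PGI-I is worded as an outcome 12 weeks after starting or switching, but it is measured from study baseline, 12.0 to 24.9 weeks after drug start

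*Protocol article*

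**What the plan says.** Under Rationale and aim of the study, the primary objective reads: "assess Patient Global Impression of Improvement (PGI-I) scores with vortioxetine at 12 weeks compared with other monotherapy antidepressant treatments following a new start or switch". Study design repeats it: the study "analyzes overall improvement with vortioxetine at 12 weeks compared with other monotherapy antidepressants following a new start or switch of treatment".

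Under Inclusion and exclusion criteria, patients in the quantitative part "should have either recently started or changed antidepressant monotherapy within the last 90 days before consent", and they "must have a baseline 9-item Patient Health Questionnaire (PHQ-9) score ≥ 5". In Table 2 the qualifying PHQ-9 sits in the screening column, so it is taken after the drug has been started or changed.

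Table 1 gives the anchor for the primary measure: "Patient baseline reflection on current depression status (baselining for PGI-I". Table 2 places consent and this reflection at study baseline and first collects PGI-I at week 12, with a window of +6 days.

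Groups are not randomised. Study population gives "targeted recruitment ratios of 2:1 for other standard of care (SOC) monotherapy to vortioxetine", with at least 378 evaluable at week 12. For confounding, the statistical paragraph offers "stratification, corresponding to the levels of potential confounders (e.g., age groups and sex) will be employed as applicable", followed by a multivariable regression whose covariates are not listed.

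**The concern.** The objective sets the clock at the start or switch of treatment. The eligibility window and the PGI-I anchor set it at study baseline. The two agree only for a patient who enrols on the day of starting. For everyone else, part of the response comes before the anchor and is not rated.

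The PHQ-9 floor adds selection. Patients who responded early enough to fall below 5 are not eligible, so those who enter late lean towards slow or partial response.

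Two things are at stake. The result may be reported as a 12-week effect of starting treatment, which this design does not measure. And how much further a patient improves after baseline depends on how long they have already been on the drug, so unequal entry timing between the groups could look like a drug difference.

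**Working it through.** **Timing (documents only).** Inputs: entry 0 to 90 days after start or switch (Inclusion and exclusion criteria); PGI-I 12 weeks after baseline, window +6 days (Table 2). Consent and baseline are taken as the same day.

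Weeks since drug start at the rating = 12 + d/7, where d is days since start at entry.

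- d = 0: 12.0 weeks
- d = 45: 12 + 6.4 = 18.4 weeks
- d = 90: 12 + 12.9 = 24.9 weeks
- d = 90 with the window: 12 + 96/7 = 25.7 weeks

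The entry window (90 days) is longer than the follow-up to the primary time point (12 × 7 = 84 days). This result needs no assumption about the drugs.

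**Response already past the anchor (assumed curve).** Suppose response is exponential with a time constant τ of 3, 4 or 6 weeks. The share complete by entry is 1 − exp(−d/(7τ)):

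| Entry day | τ = 3 | τ = 4 | τ = 6 |
|---|---|---|---|
| 30 | 76% | 66% | 51% |
| 90 | 99% | 96% | 88% |

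Under these values, at least half of the eventual response lies before the anchor for a patient entering at day 30.

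**Can the groups differ with identical drugs? (assumed throughout.)** The 378 evaluable patients split 2:1 give 378 × 1/3 = 126 and 378 × 2/3 = 252. Simulation inputs:

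- PHQ-9 at start: mean 16, SD 4
- eventual reduction: mean 50%, SD 25%, limited to 0–100%
- measurement SD of 2 on the entry score, and entry only if that score is at least 5
- PGI-I = 4 − (fall from baseline)/3 + noise with SD 1, rounded and held to 1–7
- entry times spread over 0 to 90 days
- unadjusted two-sample t-test, two-sided 5% (the article states no alpha), 1,500 repeats, τ = 3, 4, 6

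The group of 126 is given the earlier entry times.

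| Mean days since start (126 vs 252) | PGI-I difference | Rejection rate |
|---|---|---|
| 45 vs 45 | about 0 | 3.5–5.3% |
| 40 vs 50 | 0.20–0.22 | 33.7–39.9% |
| 35 vs 55 | 0.39–0.43 | 83.5–91.5% |
| 30 vs 60 | 0.58–0.66 | 99.3–99.8% |

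The PHQ-9 floor removed about 9% to 17% of patients when entry times were equal. When they were unequal, it removed more from the later-entering group (at τ = 4 and 35 vs 55 days, 10.4% vs 17.3%).

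The simulation shows a mechanism and its direction. With equal timing there is no spurious difference; with unequal timing there is one. None of the unequal timings comes from the documents.

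**The case against.** **The clock is defined.** Table 2 counts weeks from study baseline, Table 1 anchors PGI-I there, and the phrase about a new start or switch can be read as describing who is studied rather than when the clock starts. A 90-day window is a practical choice for recruiting from one online community, and a PHQ-9 floor leaves room to see improvement. This stands as a defence of the design, and it is why eligibility need not change. It does not rescue the wording: two sections put the 12 weeks directly alongside the start or switch, and a reader of the results would take them as weeks on treatment.

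**Adjustment belongs to the statistical analysis plan.** A reader might infer that only age and sex will be adjusted for. The article does not say that: age and sex are given as examples, and a multivariable regression is promised. The analysis plan, which is available on request and not shown here, may already include time since start. The absence of a covariate list is therefore not the fault. What the plan cannot change is the mismatch between the objective, the anchor and the entry window, and no regression recovers early remitters who never entered.

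**The bias is hypothetical.** This also stands. One eligibility rule applies to both groups, and the 2:1 target fixes group counts, not time on drug. The Limitations section already concedes confounding by selection and indication, though it does not mention time on drug at entry.

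**Conclusion.** The mismatch holds on the article's own text. The primary measure is improvement from study baseline, rated 12.0 to 24.9 weeks after drug start (25.7 with the visit window), in patients who had not already dropped below PHQ-9 5. That is not improvement 12 weeks after a new start or switch.

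The between-group bias is conditional. It needs the groups to differ in days since start or in the mix of new starts and switches, and the article gives no distribution of either. A reader might infer from the simulation that the primary comparison is biased by a known amount; the documents do not support that, and every simulated figure rests on assumed inputs.

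Nor can such a figure be set against the difference the study was sized to detect, because the article states no alpha, power or effect size. With an assumed 80% power, two-sided 5% and 2:1 groups, a 15-point gap gives 378 at 35% vs 50% but 302 at 20% vs 35%, so any benchmark would be another assumption.

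This should be fixed as a cheap improvement. It does not invalidate the study.

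**What to change.** Leave eligibility as it is, and make three changes.

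1. Restate the primary objective as PGI-I improvement from study baseline to study week 12 in patients who started or switched monotherapy within the previous 90 days. Add to Limitations that patients who remitted before entry are not represented.
2. In the planned multivariable model for the primary comparison, include days since start in a flexible form, new start versus switch, and entry PHQ-9. The start date is already needed to check eligibility. Entry PHQ-9 is measured after drug start, so it is a true baseline covariate only under the restated objective; this is another reason to make the first change.
3. Add a sensitivity analysis limited to patients who started or switched within about 30 days of baseline.

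The cost is a few sentences and two or three covariates derived from information collected at entry. The claim becomes narrower, and the sensitivity subset will be smaller and less precise. Adjustment deals with measured differences in timing and mix, but it does not bring back patients who responded before they could enrol.
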